## Abstract

**Background:**

Lifestyle modification is widely recommended to kidney allograft recipients post transplantation due to the cardiometabolic risks associated with immunosuppression including new-onset diabetes, weight gain and cardiovascular events. However, we have no actual evidence that undertaking lifestyle modification protects from any adverse outcomes post transplantation. The aim of this study is to compare whether a more proactive versus passive interventional approach to modify lifestyle is associated with superior outcomes post kidney transplantation.

**Methods/design:**

We designed this prospective, single-centre, open-label, randomised controlled study to compare the efficacy of active versus passive lifestyle intervention for kidney allograft recipients early post transplantation. A total of 130 eligible patients, who are stable, nondiabetic and between 3 and 24 months post kidney transplantation, will be recruited. Randomisation is being undertaken by random block permutations into passive (*n* = 65, leaflet guidance only) versus active lifestyle modification (*n* = 65, supervised intervention) over a 6-month period. Supervised intervention is being facilitated by two dietitians during the 6-month intervention period to provide continuous lifestyle intervention guidance, support and encouragement. Both dietitians are accredited with behavioural intervention skills and will utilise motivational aids to support study recruits randomised to active intervention. The primary outcome is change in abnormal glucose metabolism parameters after 6 months of comparing active versus passive lifestyle intervention. Secondary outcomes include changes in a wide array of cardiometabolic parameters, kidney allograft function and patient-reported outcome measures. Long-term tracking of patients via data linkage to electronic patient records and national registries will facilitate long-term comparison of outcomes after active versus passive lifestyle intervention beyond the 6-month intervention period.

**Discussion:**

This is the first randomised controlled study to investigate the benefits of active versus passive lifestyle intervention in kidney allograft recipients for the prevention of abnormal cardiometabolic outcomes. In addition, this is the first example of utilising behaviour therapy intervention post kidney transplantation to achieve clinically beneficial outcomes, which has potential implications on many spheres of post-transplant care.

**Trial registration:**

This study was registered with the Clinical Trials Registry on 27 August 2014 (ClinicalTrials.org Identifier: NCT02233491).

## Background

Post-transplantation diabetes mellitus (PTDM) is a common medical complication after kidney transplantation and is associated with long-term morbidity, mortality and increased cost [1]. From a patient perspective, development of PTDM is cited by kidney transplant recipients as their biggest concern post transplantation after the risk of graft loss, death and cancer [2]. In the immediate postoperative setting over 85 % of kidney allograft recipients have evidence of significant hyperglycaemia [3] and it has been estimated that, using contemporary diagnostic criteria, up to 39 % of kidney allograft recipients will develop PTDM within the first year after transplantation [1]. PTDM is common because kidney transplant recipients have both transplant-specific (e.g. immunosuppression) and nonspecific (e.g. age, ethnicity, obesity) risk factors [4]. Therefore, strategies to attenuate this high risk for developing PTDM (and other cardiometabolic risk factors such as weight gain, hyperlipidaemia and hypertension) should be actively pursued after kidney transplantation to prevent adverse long-term outcomes, although evidence that providing this advice improves clinical outcomes is lacking.

In the general population, lifestyle modification has been shown to reduce the long-term risk of developing type-2 diabetes mellitus among high-risk patients (e.g. those with pre-diabetes). Tuomilehto et al. showed how the cumulative incidence of diabetes in a lifestyle intervention group was 11 % compared with 23 % in a control group of similar characteristics, resulting in a 58 % reduction in the risk of diabetes **(hazard ratio 0.4, 95 % confidence interval 0.3–0.7,*****p*** 
**< 0.001)** [5**]**. In another study to support these findings, Pan et al. showed that diet, exercise and a diet-plus-exercise intervention was associated with a **relative risk of 0.69 (standard error 0.17,*****p*** 
**< 0.03), 0.54 (standard error 0.01,*****p*** 
**< 0.0005) and 0.58 (standard error 0.17,*****p*** 
**< 0.005),** respectively, in the risk of developing diabetes compared with the control group [6]. Finally, Lindstrom et al. demonstrated a **reduced hazard ratio of 0.57 (95 % confidence interval 0.43–0.76,*****p*** 
**= 0.00001)** secondary to lifestyle intervention [7]. Importantly, in this latter study the beneficial changes persisted after discontinuation of the intervention. Recent data has confirmed that lifestyle intervention is associated with **a reduced hazard ratio of 0.73 (95 % confidence interval 0.65–0.83,*****p*** 
**< 0.0001)** in diabetes incidence during a mean follow-up of 15 years after participation in the 3-year Diabetes Prevention Programme [8], attenuating concern regarding long-term sustainability beyond interventional study periods.

While evidence to support lifestyle modification exists in the general population, it is important to appreciate the different pathophysiology associated with the development of type-2 diabetes mellitus versus PTDM. In a multicentre collaboration, Hecking et al. analysed glycaemic parameters comparing kidney allograft recipients with individuals from the general population (both normal subjects and those with type-2 diabetes mellitus), demonstrating disparate pathophysiology favouring more pancreatic beta-cell dysfunction in the transplant cohort with PTDM [9]. Despite these differences, clinical evidence from the general population is frequently extrapolated to kidney allograft recipients and current guidance recommending lifestyle modification for all kidney allograft recipients to attenuate their risk for PTDM is one example of this [10]. However, there is a growing consensus on the urgent need for transplant-specific clinical studies due to altered risk factor patterns and reverse epidemiology being commonly described in the renal failure population [11].

We have previously demonstrated the successful use of active lifestyle modification in the setting of kidney transplantation [12]. Kidney allograft recipients with abnormal postprandial glucose metabolism on an oral glucose tolerance test (OGTT) (impaired glucose tolerance and PTDM, *n* = 36) were selected to have active lifestyle modifications (dietitian referral, a graded exercise programme and weight-loss advice), while kidney allograft recipients with normal postprandial glucose metabolism (normal and impaired fasting glucose, *n* = 79) received leaflets advocating healthy lifestyle modifications alone. In this study, patients receiving active lifestyle intervention demonstrated a significant reduction in postprandial glucose levels (10.2 mmol/L to 8.7 mmol/L, *∆* = −15 %, *p* = 0.012) and improved reclassification of glycaemic status on reevaluation by OGTT 6 months later. By contrast, simple lifestyle modification advice by leaflets alone in the group with normal glucose tolerance resulted in a significant deterioration of postprandial glucose levels (5.9 mmol/L to 6.6 mmol/L, *∆* = +12 %, *p* = 0.001) and worse glycaemic status reclassification on follow-up OGTT. The limitations of this study were the lack of randomisation and noncomparable groups (with different metabolic profiles), meaning that a direct comparison of the benefits of active versus passive lifestyle intervention was not possible. Therefore, it is difficult to ascertain whether changes in glucose metabolism were directly linked to active versus passive lifestyle intervention.

To fill this gap in the literature, and to determine transplant-specific clinical evidence, this study has been designed as the first randomised controlled trial to assess the efficacy of active versus passive lifestyle intervention in a high-risk transplant cohort to attenuate the risk of abnormal glucose metabolism. In addition to being the first clinical trial of lifestyle intervention, this randomised controlled trial is also the first example of a behaviour change protocol being utilised as part of an interventional programme to alter behaviour post transplantation, which could have potential applications beyond lifestyle intervention alone for solid organ transplant recipients. Interventions to change health-related behaviours, such as diet and exercise, are usually complex, consisting of many interacting components [13]. Furthermore, they are often poorly reported in the research literature, limiting the possibility of identifying their effective ingredients. Therefore, attention has recently been paid to the standardised reporting of intervention content and the component behaviour change techniques (BCTs) [13, 14]. The development of a taxonomy of BCTs has allowed the use of meta-analysis and meta-regression to assess the effectiveness of behaviour change interventions designed to promote physical activity and healthy eating [15–17]. This work suggests that self-regulatory techniques congruent with Control Theory [18] are significantly more effective than interventions not including these techniques. These include encouraging the individual to decide to act (intention formation), prompting specific goal setting, providing feedback on performance and self-monitoring of behaviour, and reviewing previously set goals or intentions. These techniques were combined with two other effective strategies to support the behaviour change intervention. Firstly, ‘Node-link mapping’ (NLM) is a simple visual representation system for presenting behaviour change interventions, supported by a body of educational psychology and treatment research showing that its use is more effective than standard consultation techniques for improving the therapeutic alliance, increasing focus on key issues during the session, and improving outcomes [19]. It also has an evidence base in patients with poor reading skills or working in a language other than their first language [19]. Secondly, Social Behaviour and Network Therapy (SBNT) focusses on building social network support for behaviour change by assessing the patient’s level of support from family and friends and inviting key supportive others to assist with goal setting and monitoring. Evidence supporting the validity of this intervention has been published in the liver transplant population [20] and will be translated over to a kidney transplant cohort.

In summary, this randomised controlled trial will assess the efficacy of a novel behaviour change intervention technique to encourage active lifestyle modification in nondiabetic kidney allografts recipients who are at risk for PTDM and promises to fill an important gap in the literature to guide clinical management and patient counselling.

### Specific research questions

This study is designed to answer four important questions relevant to kidney transplant recipients who are at risk of developing PTDM:Does lifestyle modification intervention improve glycaemic, cardiometabolic, clinical and physiological parameters in kidney allograft recipients?Is active dietitian-led intervention (incorporating a behaviour therapy approach) more effective than passive leaflet-driven guidance?Does active versus passive lifestyle modification improve patient-reported outcomes measures post kidney transplantation?Are there long-term clinical advantages beyond the 6-month intervention period for either active or passive groups?

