### Study protocol and interventions

Potential participants will be identified through computerised search of medical records on patients attending clinic and from clinicians in charge of outpatient services. Relevant clinic lists will be reviewed on a weekly basis and potential participants identified (first approach will be from medical team or renal research nurse). Potential participants will be given the opportunity to reflect on the information given both verbally and within the written information sheet. No fixed time is specified for the length or timing of this prior interview as it will be dependent upon the patient’s understanding of their underlying disease, transplantation and complications, as well as their understanding of the research project.

Kidney allograft recipients who fulfil the eligibility criteria and give informed consent will be subsequently randomised into active versus passive intervention arms (at which point an OGTT is performed in each patient *after* randomisation and *before* intervention) (see Fig. 1). Randomisation will be facilitated through www.sealedenvelope.com, using random permuted blocks within strata to balance numbers and characteristics, into one of the following lifestyle intervention groups (*n* = 65 for each intervention group, total 130 participants):

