**Fig. 4 Fig4:**
[figure not shown]
Intervention slide outlining patient weight goals used to support the behaviour change element of the active lifestyle intervention*Passive control group*. This group will be counselled about the risks of glucose intolerance and will receive leaflets outlining lifestyle modification advice. The leaflets include advice on healthy eating, exercise and the importance of weight loss. However, there will be no dietitian referral or focussed exercise and weight-loss monitoring review and no behaviour therapy intervention. Follow-up will be at routine clinic visits only where lifestyle modification advice will be reinforced as per usual clinical practice.

After 6 months of either intervention, both groups will undergo a repeat OGTT to assess any change in glycaemic status and metabolic physiological parameters. If any kidney allograft recipient develops PTDM during the course of the study, then they will be treated as per protocol (lifestyle modification advice with glucose-lowering therapy based upon individualised clinical assessment).

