#### Metabolic parameter assessments

Venous blood sampling from both baseline and follow-up OGTTs will be used to determine changes in insulin sensitivity, insulin secretion and the disposition index (interrelationship between both insulin sensitivity and secretion). The following formulae will be utilised for determination of these parameters of glucose metabolism:$$ \underline {Insulin\kern0.5em  secretion}=HOM{A}_{sec}= Insuli{n}_0\times \kern0.5em \left[ 3.33\kern0.1em /\kern0.1em \left( glucos{e}_0- 3.5\right)\right] $$$$ \begin{array}{ll}&{Insulin\kern0.5em  sensitivity}= McAuley's\kern0.5em  index= exp\\ &\qquad\qquad\qquad\qquad\qquad \times\left[\mathit{ 2. 6 3}-\left( \mathit{0. 2 8}\kern0.5em \times \kern0.5em  In\kern0.5em \left\{ {\mathit{insulin}}_{\mathit{0}}/ \mathit{6. 945}\right\}\right)\right.\\&\qquad\qquad\qquad\qquad\qquad-\left.\left(\mathit{ 0. 31}\kern0.5em \times \kern0.5em  In\kern0.5em  {\mathit{trigycerides}}_{\mathit{0}}\right)\right]\end{array} $$$$ \begin{array}{l}\underline {Disposition\kern0.5em  index}=HOM{A}_{sec}\times McAuley\mathit{\hbox{'}}s\kern0.5em  index= In suli{n}_0\times \left[ 3.33\kern0.2em /\kern0.1em \left( glucos{e}_0- 3.5\right)\right]\kern0.5em \times \kern0.5em \\ {} exp\kern0.5em \left[ 2.63-\left( 0.28\kern0.5em \times \kern0.5em  In\kern0.5em \left\{ insuli{n}_0/ 6.945\right\}\right)-\left( 0.31\kern0.5em \times \kern0.5em  In\kern0.5em  trigyceride{s}_0\right)\right]\end{array} $$

Surrogates for insulin sensitivity [27] and disposition index [28] have previously been validated and reported in the context of kidney transplantation. In addition to allowing us to determine the difference between active versus passive lifestyle intervention, comparison of baseline and follow-up glucose metabolic parameters will provide some insight into underlying pathophysiological mechanisms that lead to progression of abnormal glucose metabolism post transplantation.

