#### Statistical analysis

Normality of data will be assessed using the Kolmogorov-Smirnov tests. The paired sample *t* test and the Wilcoxon signed rank test, for parametric and nonparametric data, respectively, will be used to compare the means of two variables from a single group. Comparison of data between groups will be made using unpaired Student’s *t* tests and the Mann-Whitney test for parametric and nonparametric data, respectively. Categorical data will be analysed using Pearson’s or Spearman’s test as appropriate.

We will use Cox proportional hazards regression to analyse survival outcomes. Additionally, for all primary and secondary analyses, we will carry out multivariable analyses using generalised linear models (adjusting for stratification factors). In this case, we will use the corresponding odds ratio to evaluate the adjusted size of the differences between proportions, by transforming back the estimated odds ratio associated with the treatment group into absolute differences in proportions. If the results of the analysis of the primary outcome are significantly affected, the adjusted effects will be taken as final. A *p* value <0.05 will be considered significant in the statistical analysis.

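### Research question 1 asks whether lifestyle intervention works, but both arms receive lifestyle advice, so the trial can estimate only active versus passive

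*Protocol article*

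**What the plan says.** The section Specific research questions lists four questions that the study is designed to answer. The first is "Does lifestyle modification intervention improve glycaemic, cardiometabolic, clinical and physiological parameters in kidney allograft recipients". The second is "Is active dietitian-led intervention (incorporating a behaviour therapy approach) more effective than passive leaflet-driven guidance". Listed side by side, the first reads as something other than the comparison of arms.

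Under Study protocol and interventions, patients are randomised "into one of the following lifestyle intervention groups". The active arm has dietitian appointments, a graded exercise programme and behaviour therapy. Of the passive arm the article says: "This group will be counselled about the risks of glucose intolerance and will receive leaflets outlining lifestyle modification advice". Its follow-up is at routine clinics, "where lifestyle modification advice will be reinforced as per usual clinical practice".

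Statistical analysis gives two sets of simple tests for continuous outcomes:
- The paired t test and Wilcoxon signed rank test "will be used to compare the means of two variables from a single group".
- Between arms: "Comparison of data between groups will be made using unpaired Student’s" t tests or Mann-Whitney tests, with adjusted generalised linear models in addition.

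One threshold, p < 0.05, applies throughout. Metabolic parameter assessments adds that, beyond the difference between arms, "comparison of baseline and follow-up glucose metabolic parameters will provide some insight into underlying pathophysiological mechanisms".

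**The concern.** A question about the effect of lifestyle intervention as such needs a comparator without it. This trial has none: the contrast between arms shows what dietitian-led support adds to leaflets and counselling, not what lifestyle advice adds to nothing.

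The between-arm analysis answers question 2. By elimination, question 1 as a separate question falls to before-after tests within an arm. These credit to the intervention everything that changes over the six months. Patients enter anywhere from 3 to 24 months after transplantation, and time since transplantation advances together with exposure to the advice, so the two cannot be told apart within an arm.

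At stake is what the trial may conclude. A significant paired test in either arm, or in both, could be reported as the answer to question 1 although no randomised evidence bears on it.

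**Working it through.** **Step 1. What the sample size covers.** Inputs from Sample size: difference 16% (20% minus 4%), SD of change 25%, two-sided 5% level, 95% power, 65 per arm.

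- Normal approximation: n per arm = 2 × (1.960 + 1.645)² × 25² / 16² = 63.5, rounded up to 64.
- Power at 65 per arm: standard error 25 × √(2/65) = 4.39; 16/4.39 = 3.65; Φ(3.65 − 1.96) = 0.954.
- Two-sample t test: n = 64.4, rounded up to 65; power at 65 = 0.952.

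The stated 65 per arm is reproduced. It sizes active versus passive only; nothing is sized for question 1.

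**Step 2. Which analysis could serve which question.**

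| Question | Contrast needed | Available in the design? | Listed analysis |
|---|---|---|---|
| 2: active versus passive | Between the randomised arms | Yes | Unpaired tests, adjusted models |
| 1: lifestyle intervention as such | Advice versus no advice | No; both arms receive advice | Only the paired within-group tests remain |

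The last cell is an inference. The article ties the paired tests to no research question.

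**Step 3. What a paired test does when there is no intervention effect.** Suppose a background change d occurs in both arms for reasons unrelated to the intervention. With the protocol's SD of change (25%) and n = 65, the standard error is 25/√65 = 3.10 and the noncentrality is δ = d/3.10. The two-sided 5% critical value on 64 degrees of freedom is 1.998. The probability of significance is 1 − F(1.998; 64, δ) + F(−1.998; 64, δ), where F is the noncentral t distribution function.

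| Background change d | δ | Paired test significant, n = 65 | Simulated, paired | Simulated, between arms |
|---|---|---|---|---|
| 0% | 0 | 0.05 | 0.048 | 0.049 |
| 4% | 1.29 | 0.25 | 0.249 | 0.049 |
| 5% | 1.61 | 0.36 | 0.357 | 0.049 |
| 10% | 3.23 | 0.89 | 0.890 | 0.049 |

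The simulation used 20,000 trials per row. With only the 52 completers per arm implied by 20% dropout (0.80 × 65), the paired probabilities at 4%, 5% and 10% are 0.20, 0.29 and 0.81.

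**Status of d.** The size of the background change is an assumption. The values 4% and 5% are the protocol's expected control-arm change with and without dilution by dropouts. They serve only as a scale, because that arm also receives advice and the protocol gives no direction for the change. The 10% row shows how quickly the problem grows.

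**The case against.** The strongest reply is that question 1 merely names the outcome domains and question 2 supplies the contrast. The leaflet arm is called a control group and is followed under usual practice. The stated aim, the design, the sample size and the between-arm tests all concern active versus passive. This reading is possible, but it makes question 1 overlap question 2, and the trial still has no comparator without advice. The wording would need changing either way.

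It is also fair that the paired tests are listed generically. The one stated purpose of the before-after comparison is modest: some insight into mechanisms, alongside the difference between arms. This stands. The article does not say it will claim efficacy from paired tests; the point is that question 1, as posed, leaves nothing else to answer it.

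Nor does the article document a trajectory for these outcomes, and the abstract describes recruits as stable. That is why the background change is treated as an assumption and shown over a range.

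A reader might go further in two ways that the document does not support.
- **Regression to the mean.** The sponsor's earlier study chose its groups by their glucose tolerance result, so this is a natural suspicion there. Here entry requires no abnormal glycaemic value, and arms are assigned by randomisation. The only glycaemic filter, exclusion of known diabetes, could at most shift means towards worsening.
- **Comparing the arms by their separate p values.** A reader might fear that significance in one arm and not in the other will be taken as a treatment effect. Nothing in the article proposes this, and direct between-arm tests are already planned.

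**Conclusion.** The point holds as a mismatch between a stated objective and the design. Question 1, taken as distinct from question 2, cannot be answered by this trial, and no analysis can supply the missing comparator.

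If it were answered with the paired tests, a background change of 4 to 5% would give a significant result in an arm with probability about 0.25 to 0.36, and 10% about 0.89, with no intervention effect at all. These figures rest on an SD of change of 25%, 65 analysed patients per arm, approximately normal changes and an assumed background change. The use of paired tests for question 1 is inferred, not stated.

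It would be wrong to infer that the trial's main result is compromised. The randomised comparison keeps its 5% error rate under any background change common to both arms, and its sample size reproduces.

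**What to change.** - Restate question 1 as the randomised contrast of active versus passive across the glycaemic, cardiometabolic, clinical and physiological outcomes, or label it exploratory.
- In Statistical analysis, describe within-arm changes as descriptive: mean change with a 95% confidence interval for each arm, not a test of efficacy.
- Add a sentence that every efficacy conclusion rests on the between-arm estimate.

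This costs wording only; no data collection, randomisation or sample size changes. What is given up is a before-after claim that the design cannot support.
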